Any radiological signs of bone disease including osteolysis (at least 10 mm), osteopenia, halisteresis, fractures including vertebral compression fractures (these findings are not necessarily equal to a Myeloma Defining Bone Disease Event; which is defined according to the International Myeloma Working Group Consensus Statement Paris 2011). No bone disease / Bone disease can be diagnosed on either conventional radiography or low-dose CT

QoL:

Quality of Life is evaluated using the European Organization for Research and Treatment of Cancer Quality of Life Questionnaire-Core 30 (EORTC QLQ-C30, version 3.0, together with the MY20 multiple myeloma specific supplement.

Primary Endpoint:

To compare the time to PBD from year 2 to year 4 in patients treated with monthly zoledronic acid in two consecutive years compared to patients treated with monthly zoledronic acid in four consecutive years.

Secondary Endpoints:

To compare the incidence of PBD from year 2 to year 4 in patients treated with monthly zoledronic acid in two consecutive years compared to patients treated with monthly zoledronic acid in four consecutive years.

To compare the incidence of sPBD from year 2 to year 4 in patients treated with monthly zoledronic acid in two consecutive years compared to patients treated with monthly zoledronic acid in four consecutive years.

To compare the incidence of bone healing from year 2 to year 4 in patients treated with monthly zoledronic acid in two consecutive years compared to patients treated with monthly zoledronic acid in four consecutive years.

To compare the overall survival from year 2 to year 4 in patients treated with monthly zoledronic acid in two consecutive years compared to patients treated with monthly zoledronic acid in four consecutive years.

To compare the incidence of BON from year 2 to year 4 in patients treated with monthly zoledronic acid in two consecutive years compared to patients treated with monthly zoledronic acid in four consecutive years.

To compare the development in QoL from year 2 to year 4 in patients treated with monthly zoledronic acid in two consecutive years compared to patients treated with monthly zoledronic acid in four consecutive years.

To compare the development in the bone markers CTX-I, PINP, bALP, and TRAP5b from year 2 to year 4 in the patients groups randomised to receive two or four years of treatment with zoledronic acid

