To investigate if monthly measurements of the bone markers CTX-I, PINP, bALP, TRAP5b, or the ratios of these can be used to predict the development of PBD from year 2 to year 4.

To investigate the consistency between the finding “no bone disease” when using conventional radiography compared to low-dose CT at diagnosis*.

To investigate if the patients with inconsistency in bone disease status using the different imaging modalities at diagnosis are more likely to progress in bone disease compared to patients diagnosed with “no bone disease” using both modalities*.

To investigate if the three patients groups 1. consistent “no bone disease” 2. inconsistent bone disease 3. consistent “bone disease”, at diagnosis can be identified using the levels of the bone markers CTX-I, PINP, bALP, TRAP5b, ICTP, or the ratio of these.

* Sites may participate in the study without conduction both conventional radiography and low-dose CT.

Amendment: The primary endpoint will not be affected by the amendment. The eight first secondary endpoints will not be affected by the amendment. The last three secondary endpoints will be affected by the amendment, but it is without statistical relevance; see section 1.13

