Sites may participate in the study even if they only evaluate bone disease using either conventional radiography or low-dose CT. Since this part of the study is mainly descriptive, no statistical cut-off values have been defined. We expect however, that at least half of the patients will be evaluated using both modalities. All patients will have bone imaging conducted at the time points specified in appendix 1. Each patient will function as his or her own control since we will look for discrepancies between the different modalities, and the development in these discrepancies over time. Data will be analysed using the student t-test.

Amendment: The amendment will have no impact on the statistical consideration since all patients will be randomised. Only the part of the study comparing low-dose CT to conventional radiography will be affected. This part of the study however is descriptive and each patient function as his or her own control no statistical changes need to be made.

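### The Student t-test named for the radiography versus low-dose CT comparison cannot measure consistency of a yes/no finding (minor)

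*Protocol*

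**What the plan says.** The imaging paragraph under Other endpoints in Protocol section 1.13 describes a within-patient comparison: "Each patient will function as his or her own control since we will look for discrepancies between the different modalities". The same sentence adds how those discrepancies develop over time. The paragraph then closes with "Data will be analysed using the student t-test". It gives neither the form of the test (paired or two-sample) nor the variable to be tested. It also calls this part mainly descriptive, sets no cut-off values, and says of coverage: "We expect however, that at least half of the patients will be evaluated using both modalities".

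Section 1.5 defines the finding as a two-category status read on each modality: "No bone disease / Bone disease can be diagnosed on either conventional radiography or low-dose CT". Three secondary endpoints use it:

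- consistency of a no-bone-disease finding "when using conventional radiography compared to low-dose CT at diagnosis";
- whether patients with inconsistent findings "are more likely to progress in bone disease compared to patients diagnosed with" no bone disease on both modalities;
- whether the three resulting groups "at diagnosis can be identified using the levels of the bone markers CTX-I, PINP, bALP, TRAP5b, ICTP, or the ratio of these".

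The protocol defines no lesion count or continuous imaging score for comparing the modalities.

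**The concern.** A t-test compares means. Applied to a status coded 0 or 1, it compares the proportion positive on CT with the proportion positive on radiography. The endpoint asks something else: how often the two readings of the same patient agree. Two modalities can have equal positivity rates and still disagree in many patients, because disagreements in opposite directions cancel in the difference of means.

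Section 1.4 lists replacing radiography by low-dose CT as the standard as one of the study's three purposes. Section 1.14 cites that question among the reasons for the additional imaging. If the stated method were followed literally, the reported result would not answer the consistency question. The p-value would also depend on a choice, paired or unpaired, that the text leaves open.

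**Working it through.** The protocol gives no sample size, power or p-value for this comparison, so there is no figure of its own to reproduce. The check matches the named test to the data type and then applies it to assumed tables.

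**Inputs.** Section 1.13 gives 358 patients to be included, at least half with both modalities: 358 / 2 = 179. The documents give no discordance counts, so every 2×2 table below is an assumption. Notation: a = both positive, b = CT positive only, c = radiography positive only, d = both negative, n = a + b + c + d.

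**Formulas.**
- Difference in positivity = (b − c)/n. This is the numerator of both the paired and the unpaired t-test.
- Exact McNemar: two-sided binomial test of b out of b + c against 0.5.
- Kappa = (Po − Pe)/(1 − Pe), with Po = (a + d)/n and Pe = m1·m2 + (1 − m1)(1 − m2), where m1 = (a + b)/n and m2 = (a + c)/n.

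**Step 1: can the test see agreement?**
- Table 139/2/2/36: Po = 175/179 = 0.978, m1 = m2 = 141/179 = 0.788, Pe = 0.666, kappa = 0.312/0.334 = 0.93. Difference = 0, so p = 1.00 for both forms of t-test.
- Table 60/40/40/39: Po = 99/179 = 0.553, m1 = m2 = 100/179 = 0.559, Pe = 0.507, kappa = 0.046/0.493 = 0.09. Difference = 0, so again p = 1.00 for both forms.

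Discordance is 4/179 = 2.2% in the first table and 80/179 = 44.7% in the second, and the named test returns the same result. McNemar's test also gives p = 1.00 in both, since it too addresses the difference in rates. What separates the tables is the discordance proportions and kappa.

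**Step 2: does the paired or unpaired form matter?** Table 139/11/2/27: CT positive 150/179 = 83.8%, radiography positive 141/179 = 78.8%, difference 9/179 = 5.0 points, kappa 0.76. The radiography rate was set near the 79% with abnormal radiographs at diagnosis quoted in section 1.3 from a published series; the CT rate and the 11/2 split are assumed.

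| Method | p |
| --- | --- |
| Unpaired t-test | 0.22 |
| Paired t-test | 0.012 |
| Asymptotic McNemar, (11 − 2)²/13 = 6.23 | 0.013 |
| Exact McNemar, 11 of 13 | 0.022 |

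**Step 3: few discordant pairs.** Table 140/5/0/34: paired t-test p = 0.025; exact McNemar p = 2 × 0.5⁵ = 0.063. Here the paired t-test crosses 0.05 and the exact test does not.

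**The case against.** The strongest reply is that section 1.13 says each patient serves as his or her own control, and the amendment text in that section repeats it. The paired form is therefore the natural reading, and on 0/1 data a paired t-test is nearly the asymptotic McNemar test (0.012 against 0.013 in step 2). This stands. A reader might infer that the plan discards the pairing and will miss a real difference in detection. The text does not support that: it never says unpaired, and the result of 0.22 arises only under that reading. Under the paired reading the remaining numerical risk runs the other way, towards being too liberal when discordance is sparse.

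A reader might also infer that the t-test is prescribed for every imaging endpoint. That is not established. The sentence is tied to discrepancies between modalities and their development over time. It does not say that progression in inconsistent versus consistent patients will be tested this way, and a method left unstated there may sit in the statistical analysis plan. For the marker endpoint, pairwise t-tests on continuous levels would be insufficient for a three-group identification question rather than invalid.

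Naming a test also does not prevent discordance counts from being reported, and this part is secondary and mainly descriptive. Both points stand and limit the weight of the concern. They do not rescue the sentence: the only method it names does not answer the consistency endpoint, and a descriptive aim calls for estimates of agreement.

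**Conclusion.** Wrong as written, minor. The protocol does not merely leave the method open; it names one that cannot measure within-patient consistency of a binary finding. That conclusion holds for either form of the t-test and depends on no assumed count: the numerator of the test is (b − c)/n, whatever the amount of disagreement.

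The p-values are illustrations on assumed tables. The figure of 179 may also be too high for the diagnosis endpoints: patients entering under the amendment are imaged around inclusion, after 23 to 25 infusions, rather than under the protocol at diagnosis, and section 1.5 acknowledges that the last three secondary endpoints are affected. Smaller numbers would make sparse discordant pairs more likely. The primary endpoint, the sample size and the data collected are unaffected.

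**What to change.** Replace the t-test sentence in section 1.13. For the paired status at diagnosis, report the proportion of patients discordant in each direction (CT positive only, radiography positive only) with 95% confidence intervals, report kappa as the agreement measure, and use the exact McNemar test for the difference in detection. If the sentence was also meant to cover progression in patients with inconsistent findings versus those with no bone disease on both modalities, say so and name a log-rank test or Fisher's exact test for it.

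The cost is one or two sentences in the protocol or the statistical analysis plan. No extra imaging, patients or visits are needed.

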**1.14 Ethical Considerations**

Multiple myeloma remains an incurable malignant disorder; however the average expected lifetime is increasing due to improved treatment. Treatment monthly with zoledronic acid is known to reduce the risk pathological fractures, progressive osteolysis, and to reduce pain. No knowledge exists on what should be done after two years of treatment. Prolonged treatment carries the risk of BON, whereas discontinuation of treatment probably increases the risk of PBD. The primary purpose of the study is to investigate if prolonged treatment with zoledronic acid provides adequate protection against PBD to justify an increased risk of BON. To investigate this, patients will be randomized 1:1 to receive either 2 or 4 years of treatment. To protect participating patients from both under- overtreatment, routine oral cavity examinations and bone imaging are planned in the protocol. Bone imaging is balanced between early detection of PBD (and thus possible removal from the protocol) and minimal radiation exposure. It is estimated that a patients will receive an excess radiation dose of 33.2 – 36.6 mSv equal to the dose received from 1.5 conventional CT. This radiation exposure is not ignorable. The median age of a newly diagnosed patient however is approximately 70 years, they all suffer from an incurable cancer and have a severely reduced life expectancy. This reduces the long-term risk of secondary malignancies due to radiation exposure to approximately 0.0175%. Furthermore, the additional bone imaging will not only help us decide if the more sensitive modality low-dose CT in the future should replace conventional radiography, it will also help determining if serum samples partly can replace bone imaging, thus reducing future radiation exposure. Most importantly, it will in the actual patient help us detect progressive bone disease before this becomes symptomatic due to e.g. vertebral collapse or pathological fractures.

An additional part of the study is to investigate if serum bone markers can be used to tailor treatment with zoledronic acid in the individual patients in the future. To investigate this, extra serum will be collected and stored for later analysis. This extra serum will be collected when blood samples to monitor the myeloma disease are collected anyway, thus no additional appearances at the outpatient clinic for blood draws over the course of the study are anticipated.

REGULATORY ETHICS COMPLIANCE

The site investigator is responsible for ensuring that the clinical study is performed in accordance with the protocol, Good Clinical Practice (GCP), and applicable regulatory requirements at the given site.

Before the start of the study in a country, the national investigator will provide the national ethical committee with current and complete copies of the following documents:

• Final protocol and, if applicable, amendments

• Written patient information, informed consent form and quality of life questionnaires

• Any other documents that the ethical committee requests to fulfil its obligation

This study will be undertaken only after the ethical committee and the National Health and Medicines Authority have given full approval of the final protocol, any amendments, the informed consent form and applicable recruiting material, and the sponsor has received a copy of this approval. This approval letter must be dated and must clearly identify the documents being approved.

PATIENT INFORMATION AND INFORMED CONSENT

Each patient must give written consent after the nature of the study has been fully explained. The consent form must be approved by the ethical committee. The informed consent should be in accordance with principles that originated in the Declaration of Helsinki, current ICH and GCP guidelines, and applicable regulatory requirements.

Before entry into the study, the site-investigator or an authorized member of the investigational staff must explain to potential patients the aims, methods, reasonably anticipated benefits, and potential hazards of the study, and any discomfort it may entail. Patients will be informed that their participation is voluntary and that they may withdraw consent to participate at any time. They will be informed that choosing not to participate will not affect the treatment of his/her disease and will not prejudice future treatment. The patient will be given sufficient time (in most cases one day or longer) to read the informed consent form and the opportunity to ask questions. After having obtained the consent, a copy of the informed consent form must be given to the patient.

Based on a total assessment, it is the opinion of the steering committee that carrying out the study is ethically warranted.

Amendment: Patient included according to the protocol will be exposed to less radiation, thus the amendment should pose no ethical problems.

**1.15 Privacy of Personal Data and Data Handling**

Each patient will be assigned a personal identification number on inclusion. The data will be archived in accordance with GCP rules for 5 years in Denmark and Norway and for 10 years in Sweden following completion of the study. The collection and processing of personal data from patients enrolled in this study will be limited to

those data that are necessary to investigate the efficacy, safety, quality, and utility of the study drugs

used in this study.

The data will be recorded on case report forms (CRF). Patients will receive a protocol number for the CRF. A patient log which may pair the protocol number with the civic registration numbers will be kept under lock and key at the sponsor’s research facility. Since this is not a blinded study decoding of the patients will probably not be necessary. However if a situation arises where it is deemed in the best interest of the patient to break to code, this will have to be decided by the national investigator or the sponsor.

Bone markers will not be measured locally. Instead serum samples collected during the study will be stored locally and then later sent to The Haematological Research Unit in Odense, Denmark. Bone markers measured bi-annually will be analysed for all patients. As stated in section 1.13 32 cases and 32 controls will be selected and monthly bone markers will be analysed 6 months retrospectively in these patients. The serum samples are collected for this specific purpose and no in order to created a research biobank. For further details on the bone markers see appendix 2.

Radiological data will be mailed to The Haematological Research Unit in Odense, Denmark. They will be kept there for later review, as specified in appendix 3.

**1.16 Access to Source Data**

Sponsor, investigators, auditors, study nurses at participating departments, the national medicines agencies, the national data protection agencies, and the national committees on research ethics may be given access to the source data.

**1.17 Publication Policy**

Both positive and negative results will be publish in the best available international medical journal in order to obtain the widest possible impact. Authorship will be decided according to the ICMJE 2013 guidelines.

**1.18 Data Quality Assurance**

The project will be monitored by the national GCP unit in Denmark and by FoU-centrum, Kliniskt prövningsstöd, Skånes Universitetssjukhus – Lund, in Sweden and Norway

**1.19 Funding**

Treatment with zoledronic acid in multiple myeloma has already received EMEA approval and is an established treatment in all the participating countries. There has been no commercial interest from the pharmaceutical companies to participate in this study. A possible outcome of the study could be that the patients should receive less treatment with zoledronic acid. External funds will be applied for to cover the expenses in the study.

**1.20 Timescale**

Initiation is expected to occur end 2014, and due to new data inclusion will end 01.12.2020 with a follow up two years the expected termination date is 01.12.2022.

An interim analysis will be conducted at the end in inclusion. The steering committee will then decide if the positive effect of a decrease in the number of PBD outweighs a negative effect of an increased risk of BON, or if the study should be terminated.

**1.21 Insurance**

The patients are insured according to national standards. It is the responsibility of the national investigators to make sure the formalities are in place before patients are included in the respective country.

